### Sample size

2.2

The sample size was based on rMSSD index^[36]^ because it presents the highest sample number necessary for this study, compared with the other main variables [6 minutes walking test^[37]^ and tumor necrosis factor (TNF)-alpha^[38]^]. A standard deviation of 17 ms, alpha risk of 5%, and beta of 80% was considered for the calculus, which resulted in 44 subjects.

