### Signals and symptoms identification

2.11

For the identification of the signals and symptoms during the CRP, a record is going to be prepared for each patient, containing the additional personal data, clinical diagnosis, use of medicines, and the signals and symptoms commonly found during CRP.

The most prevalent signals and symptoms found during CRP are symptoms: fatigue, muscle pain, angina, dizziness, nausea, and cramp; and signals: changes in pulse rate, increased systolic blood pressure during the exercise, increased diastolic blood pressure during the exercise, tachypnea, and pallor.

The signals are going to be observed and identified by previously trained professionals, and the symptoms are going to be referred to and/or confirmed by the patient at the end of the session. The observation of signals and symptoms is going to be performed during all phases of the session (initial rest, warm-up, resistance, and cooling down).

When the changes in pulse rate have been observed, the patients are going to perform the session with an electrocardiogram and the tracing is going to be recorded and analyzed to identify the rhythm disorder presented.

The evaluation of signals and symptoms is going to be performed during the 24 sessions. The symptomatology is going to be counted per session, regardless the number of times that the same signal/symptom occurs during the session.

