### Data analysis

2.12

The normality of data is going to be analyzed using Shapiro--Wilk test. According to the distribution, the population characteristics will be presented, as mean and standard deviation for parametric distribution and median and interquartile interval for nonparametric distribution.

The relationship between the number of signals and symptoms of the patients and the scale degree of the protocols (1, 2, and 3) is going to be analyzed using Pearson correlation. The concordance degree of each protocol with the number of signals and symptoms are going to be determined using coefficient of intraclass correlation. To determine the efficacy of the risk stratification protocols as soon as clinical, physical, and biochemical parameters to previse signals and symptoms during the CRP, analysis of sensibility and specificity using ROC curve is going to be done. The sensibility, specificity, and predictive value (positive and negative) for the occurrence of events are going to be also registered. If the values of the area on the curve are ≥0.650, it will be considered significative.

To evaluate whether the clinical, physical, and biochemical modifications have influenced in the occurrence of signals and symptoms, the sphericity of the data will be verified by Mauchly test, and if the sphericity be violated, Greenhouse--Geiser correction will be performed. The comparison between the different moments of the clinical (cardiorespiratory parameters and autonomic modulation), physical (maximum isometric endurance, MIVC, cardiorespiratory fitness and physical activity level), and biochemical (IL-6, TNF-alpha, and IL-10) are going to be realized by repeated measures analysis of variance (ANOVA) and the possible differences between the moments will be performed by Bonferroni post-hoc.

The statistical significance difference adopted is going to be fixed in 5% with 95% of confidence interval. The analysis is going to be done on SPSS 15.0 version (SPSS Inc., Chicago, IL).

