## Final considerations

3

As final considerations, we need to highlight the innovation of this study, which is going to be the first to investigate the efficacy of different stratification protocols and clinical, physical, and biochemical parameters to previse signals and symptoms during the CRP. Their realization will permit new study perspectives and to answer important questions that will help researchers and clinics that work with CRP. Considering the high prevalence of signals and symptoms observed in CRP, identifying the stratification protocols able to previse the appearance of these signals and symptoms will allow the physical therapist to define the most adequate risk stratification protocols, permitting more efficacy and security during these programs.

In addition, some patients who perform CRP do not have recent medical tests, which cannot enable an adequate risk stratification based on the stratification protocols proposed at the literature. In this sense, if clinical, physical, and biochemical variables, obtained at rest, will be related with the appearance of signals and symptoms during the CRP, it will also allow more efficacy and safety for the realization of CRP, mainly because these variables are at easy access and utilization.

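### Clinical, physical and biochemical markers are judged only against a yes/no event although sign and symptom counts are collected over 24 sessions; a rate-based rank concordance should be added and the ROC event fixed in advance

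*Protocol article*

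**What the plan says.** Section 2.11 lists 11 items, six symptoms and five signs. They include fatigue, muscle pain and "increased systolic blood pressure during the exercise, increased diastolic blood pressure during the exercise", with no amount of increase given. Each item is counted at most once per session, and "The evaluation of signals and symptoms is going to be performed during the 24 sessions", so every patient yields a count.

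Section 2.12 relates that count to the risk protocols by Pearson correlation and by an intraclass correlation coefficient. For the protocols and also for the clinical, physical and biochemical parameters it then plans ROC curves, with an area of 0.650 or more treated as significant. On the remaining measures it says: "The sensibility, specificity, and predictive value (positive and negative) for the occurrence of events are going to be also registered". It names no other binary outcome. The repeated-measures ANOVA compares the parameters between time points and does not relate them to the count.

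The Introduction sets two relevant questions: whether the parameters measured at rest correlate with signs and symptoms, and whether a cut-off can be found for them.

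On size, section 2.2 says "The sample size was based on rMSSD index", "which resulted in 44 subjects".

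**The concern.** A patient with one episode of fatigue in 24 sessions and a patient with angina or dizziness in most sessions give very different counts. A yes/no event may place them in the same group. For the parameters, no planned analysis keeps that difference, although the Introduction asks for their correlation with signs and symptoms.

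The split into cases and controls is also left to chance. The sample size was not derived from the ROC, so nothing secures a workable number of controls. With few controls:

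- the AUC is imprecise, and the 0.650 line is easily crossed by a marker with no information;
- specificity and NPV rest on a handful of patients;
- PPV is high whatever the marker does.

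**Working it through.** **The plan's own figure.** The 44 patients cannot be reproduced, because section 2.2 gives an SD of 17 ms, 5% alpha and 80% (read here as power) but no difference. Back-solving for a two-sided paired comparison gives (1.960 + 0.842) × 17 / √44 = 7.2 ms. No number of cases or controls enters.

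**Inputs.** From the article: 44 patients, 24 sessions, AUC line 0.650. Assumed, because the article gives no rate and no case rule: a case is a patient with at least one listed item, and p is the per-session probability of any listed item.

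**Expected controls.** With independent sessions and equal risk, controls = 44 × (1 − p)^24. With patients differing in risk (beta-binomial, mean m, between-patient intraclass correlation ρ), controls = 44 × B(a, b + 24) / B(a, b), where a = m(1 − ρ)/ρ and b = (1 − m)(1 − ρ)/ρ.

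| Per-session rate | Cases, independent | Controls, independent | Controls, ρ = 0.1 | Controls, ρ = 0.3 | Controls, ρ = 0.5 |
|---|---|---|---|---|---|
| 5% | 71% | 12.8 | 23.9 | 32.2 | 36.4 |
| 10% | 92% | 3.5 | 12.7 | 23.5 | 29.9 |
| 20% | 99.5% | 0.2 | 3.4 | 12.1 | 19.9 |
| 50% | 100% | 0.0 | 0.0 | 1.3 | 5.0 |

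At 20% with independent sessions, the chance of no control at all is 0.9953^44 = 81%. At 5% with ρ = 0.5 the imbalance reverses and only 44 − 36.4 = 7.6 cases are expected.

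**Precision with 40 cases and 4 controls.** Hanley-McNeil at AUC A = 0.65: Q1 = A/(2 − A) = 0.4815, Q2 = 2A²/(1 + A) = 0.5121, A² = 0.4225.

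- Variance = [0.2275 + 39 × 0.0590 + 3 × 0.0896] / 160 = 0.0175, so SE = 0.132 and the 95% interval is 0.65 ± 0.26, or 0.39 to 0.91.
- For a useless marker, SE = √(45 / (12 × 160)) = 0.153. The chance of AUC ≥ 0.650 is 1 − Φ(0.15/0.153) = 16%.
- With 22 cases and 22 controls, the corresponding figures are 0.49 to 0.81 and 4.4%.

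**Predictive values.** A marker unrelated to the outcome has PPV equal to prevalence, 40/44 = 0.91, and NPV 4/44 = 0.09. Specificity can only move in steps of 1/4.

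**Unequal exposure.** Section 2.1 excludes patients below 30% attendance. If that applied to the 24 sessions (an assumption), a patient could stay in with 8. At p = 10%, the chance of at least one item is 1 − 0.9^8 = 57% with 8 sessions and 92% with 24. An ever/never outcome would then partly measure attendance; a rate per attended session would not.

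**What a rank measure uses.** Without ties, the null SE of Kendall's tau over 44 patients is √[2 × 93 / (9 × 44 × 43)] = 0.105, which is 0.052 on the 0-to-1 concordance scale. The estimand differs and ties will widen it, so this is not a like-for-like gain. It does show that all 44 patients contribute, whatever the case split.

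**The case against.** The strongest reply is that the article never states an at-least-once rule. A cut-off on the count, an item-by-item ROC or a session-level ROC would all fit its wording. The full protocol may define the event and each sign, and a condensed article cannot be faulted for leaving that out. That stands: the missing definition is not itself the finding.

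A reader might infer that any exercise rise in blood pressure counts, so that nearly every patient is a case and the ROC has almost no controls. The article does not support this. It does not say *any* rise. The signs are identified by trained professionals, and the neighbouring pulse-rate item leads to an electrocardiogram to identify a rhythm disorder, which suggests abnormal findings are meant. The phrase "Considering the high prevalence of signals and symptoms observed in CRP" is a general remark about such programs, without a figure or a unit. Equal risk across patients also sits badly with a study of prediction, and allowing for differences leaves many more controls at 5% and 10%.

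It is also fair to say that the count is kept in the Pearson and intraclass analyses and that the decision line is on the AUC, not on PPV. The first part covers only the risk protocols. For the parameters the binary analyses are all there is, and that part of the concern is unanswered.

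**Conclusion.** The point holds as a weakness in the choice of analysis. For the clinical, physical and biochemical parameters, the plan tests the link with signs and symptoms only through a binary outcome, although a count over 24 sessions is at hand and the Introduction asks for a correlation.

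The size of the damage is conditional. Under a per-patient, at-least-once rule, expected controls run from 12.8 to 0.2 of 44 for per-session rates of 5% to 20% with independent, equal-risk sessions. With an intraclass correlation of 0.3 they run from 32.2 to 12.1. The rates, the rule and the correlation are assumptions. The 40/4 figures illustrate one end of that range and do not forecast the study's result. The remedy is worthwhile under any case definition, because it does not depend on how the split falls.

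**What to change.** 1. For both the risk protocols and the parameters, add as the main discrimination measure a rank concordance (Somers' D or c-index, with confidence interval) against the number of sessions with a sign or symptom divided by sessions attended. It needs no dichotomy. Read it by its interval; the 0.650 line was set for an AUC and should not be carried over.
2. Keep the ROC, sensitivity, specificity and predictive values for the cut-off question. Fix the event and its unit before analysis, for example a patient-level rate above a pre-stated value, or a session-level analysis that allows for clustering within patients.
3. Report the number of cases and controls beside every AUC and predictive value.
4. The investigators should state the recording criterion for each sign. No limit is proposed here.

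The data collected stay the same. The cost is a few sentences in the plan and a little more analysis. If a rate above a stated value is chosen, sensitivity and specificity will refer to frequent events and no longer to any event, and the report should say so.

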**Materials and methods:**

The study was prospectively registered at ClinicalTrials.gov (NCT03446742). Forty-four patient participants of a CRP will be evaluated. First, their risk stratification is going to be performed by 2 evaluators and their clinical, physical, and biochemical parameters are going to be measured. Then, the patients are going to be followed during 24 sessions during their CRP routines in order to identify appearance of their signals/symptoms. So, the patients are going to perform their cardiovascular rehabilitation routines for 6 months and then, their clinical, physical, and biochemical parameters are going to be measured again and they are going to be followed during 24 sessions during their CRP routines in order to identify the appearance of their signals/symptoms.

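### The rule that an AUC of at least 0.650 is significant is not a 5% test and can contradict the 5%/95% CI criterion in the same section

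*Protocol article*

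**What the plan says.** Section 2.12 (Data analysis) uses ROC curves for one of the study's main questions: "To determine the efficacy of the risk stratification protocols as soon as clinical, physical, and biochemical parameters to previse signals and symptoms during the CRP". It then gives the decision rule for those curves: "If the values of the area on the curve are ≥0.650, it will be considered significative". The section closes with a general criterion: "The statistical significance difference adopted is going to be fixed in 5% with 95% of confidence interval". Nothing links the two.

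The Abstract gives the size of the cohort: "Forty-four patient participants of a CRP will be evaluated". Section 2.2 (Sample size) states that "The sample size was based on rMSSD index", so the number was not chosen for the precision of an AUC. The risk protocols enter the analysis as three-grade scores (sections 2.6 and 2.12). Most of the clinical, physical and biochemical parameters are continuous.

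**The concern.** The section holds two criteria for the same result. One looks only at the AUC estimate. The other is a 5% level with a 95% interval, which depends on how many patients have events and how many do not. When they disagree, a marker is significant under one and not under the other, and the plan does not say which is reported.

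The Introduction asks whether the protocols and parameters can predict signs and symptoms during sessions. The Final considerations section expects the answer to guide the choice of stratification protocol. If the 0.650 rule is followed as written, a marker whose interval includes 0.5 can be reported as a significant predictor.

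**Working it through.** **Inputs.** N = 44 (Abstract; section 2.2). Cut-off 0.650, level 5% and 95% CI (section 2.12). Sidedness is not stated; I take it as two-sided and give the one-sided result where it differs. The split between patients with and without events is not stated, so I assume a range from 22/22 to 40/4 (with/without). The Final considerations section expects signs and symptoms to be common, so a majority with events is plausible. Section 2.1 excludes patients with attendance under 30%, so the analysed number may be below 44.

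**The plan's own figure.** Section 2.2 states: "A standard deviation of 17 ms, alpha risk of 5%, and beta of 80% was considered for the calculus, which resulted in 44 subjects". No difference to detect is given, so 44 can be neither confirmed nor refuted. Reading the 80% as power and solving backwards for a paired comparison gives (1.960 + 0.842) × 17 / √44 = 7.2 ms. This says nothing about the precision of an AUC.

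**Step 1: test of an AUC of 0.650 against 0.5, untied marker.** The null standard error is SE0 = √[(n1 + n0 + 1) / (12 n1 n0)]. At 22/22 this is √[45 / (12 × 484)] = 0.0880. Then z = 0.150 / 0.0880 = 1.70 and two-sided p = 0.088. The AUC needed is 0.5 + 1.96 × 0.0880 = 0.673.

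**Step 2: 95% CI at 0.650 (Hanley-McNeil).** With A = 0.65, q1 = A/(2 − A) = 0.4815 and q2 = 2A²/(1 + A) = 0.5121. The variance is [A(1 − A) + (n1 − 1)(q1 − A²) + (n0 − 1)(q2 − A²)] / (n1 n0). At 22/22: (0.2275 + 21 × 0.0590 + 21 × 0.0896) / 484 = 0.00692, so SE = 0.0832 and the CI is 0.650 ± 0.163.

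**Step 3: chance that a useless untied marker passes**, from the exact Mann-Whitney null distribution.

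| With/without events | SE0 | Two-sided p at 0.650 | 95% CI at 0.650 | AUC at which this CI first excludes 0.5 | AUC needed for p < 0.05 | Useless marker passes, direction fixed | Direction chosen from data |
|---|---|---|---|---|---|---|---|
| 22/22 | 0.088 | 0.088 | 0.487–0.813 | 0.661 | 0.673 | 4.4% | 8.9% |
| 33/11 | 0.102 | 0.14 | 0.471–0.829 | 0.673 | 0.699 | 7.3% | 14.5% |
| 35/9 | 0.109 | 0.17 | 0.460–0.840 | 0.682 | 0.714 | 8.7% | 17.4% |
| 40/4 | 0.153 | 0.33 | 0.391–0.909 | 0.726 | 0.800 | 17.6% | 35.1% |

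For an AUC of 0.650 to reach two-sided p = 0.05, about 58 patients are needed at a 1:1 split, 78 at 75:25, 90 at 80:20 and 156 at 90:10.

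**Step 4: three-level protocols.** Ties shrink the null variance: (N + 1) is replaced by (N + 1) − Σ(t³ − t)/[N(N − 1)], where t is the number of patients in each class. With assumed classes of 4, 9 and 31 patients at 22/22, Σ(t³ − t) = 60 + 720 + 29,760 = 30,540. Dividing by 44 × 43 = 1,892 gives 16.14. So SE0 = √[(45 − 16.14) / 5,808] = 0.0705 and the AUC needed is 0.638. Here an AUC of 0.64 would be significant at 5% yet fail the 0.650 rule, so the two criteria can disagree in both directions.

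Simulated pass rates for a useless three-level score (fixed direction / either direction):
- equal thirds at 22/22: 3.5% / 6.7%
- equal thirds at 35/9: 7.3% / 14.6%
- 80% of patients in one class at 22/22: about 0.6% / 1.3%

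**The case against.** The strongest defence is that the word *significative*, in an article whose English reads as translated, may mean useful discrimination, with the 5% level governing the tests. The text does not say this, and the same section uses the language of significance for its 5% level. If it was meant, the word still has to be corrected.

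Several stronger readings are tempting, and the documents do not support them:

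- A reader might infer that every AUC the rule passes has an interval including 0.5. That holds only at 0.650 and just above. For an untied marker the Hanley-McNeil interval excludes 0.5 from about 0.66 (22/22) to 0.73 (40/4).
- A reader might infer that 0.650 can never be significant with 44 patients. It can for a tied three-level score (Step 4). Also, the article does not state sidedness: one-sided, an untied marker at 22/22 needs only 0.5 + 1.645 × 0.0880 = 0.645.
- A reader might infer that the rule always passes useless markers far more often than 5%. At 22/22 with direction fixed, the rate is 4.4%. The risk protocols have a natural direction (low to high risk), and nothing states that direction will be chosen from the data for the other parameters.
- A reader might multiply one error rate by all protocols and parameters to get a count of false findings. That treats the three-level protocols as untied and assumes free direction for every marker, so no such count is offered here.

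The lack of a multiplicity procedure is not held against the article, since such detail may sit in a full protocol or SAP that is not shown. What remains is a conflict within the stated text, which does not depend on omitted detail.

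**Conclusion.** The point holds in a limited form. The 0.650 cut-off is not a 5% test, and it can disagree with the 5%/95% CI criterion in its own section. For an untied marker in 44 patients, an AUC of exactly 0.650 is not significant at two-sided 5% at any of the splits tried, and the most favourable one gives p = 0.088. The error rate of the rule is not one number. For an untied marker it runs from about 4.5% to 18% with direction fixed and from about 9% to 35% with direction chosen from the data; for a three-level protocol it can fall below 5%. These figures rest on the assumed event splits, on all 44 patients being analysed and, for the protocols, on assumed class distributions. The conflict between the two rules rests on none of these assumptions.

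**What to change.** Remove 0.650 as the criterion of significance in section 2.12. Judge each AUC by its 95% CI or by a test against 0.5 at the stated 5% level, corrected for ties for the three-level protocols, with the direction of each marker fixed in advance. Name one of the two as governing, because they can differ slightly: at 22/22 the Hanley-McNeil interval excludes 0.5 from 0.661, while the test needs 0.673. State that the level is two-sided if that is intended. If 0.650 is wanted, keep it as a separately labelled minimum-usefulness threshold and describe it in words other than significance.

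The cost is a change of wording and a few more output columns; no new data are needed. The downside is that fewer predictors may be declared significant.

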Taken together, these data point to some gaps in the literature. How are the risk stratification protocols effective to previse signals and symptoms during the CRP? Can clinical, physical, and biochemical parameters be used to previse signals and symptoms during the CRP? If yes, is it possible to establish a cut-off point for these parameters that can better previse the appearance of signals and symptoms in these programs? Are changes in clinical, physical, or biochemical parameters induced by CRP accompanied by changes in the appearance of signals and symptoms during the CRP?

This study was designed to answer these questions: to evaluate the risk stratification protocols efficacy to previse signals and symptoms during the CRP; to analyze the correlation between clinical, physical, and biochemical parameters, measured at rest, with the presence of signals/symptoms in CRP participants; and to evaluate whether changes in clinical, physical, or biochemical parameters, induced by CRP, will influence the appearance of signals and symptoms during these programs.

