### Study design

2.4

This study is going to be divided in 3 phases. Initially, all the volunteers are going to have their medical records analyzed, and information about the sample characterization and medical examinations are going to be extracted. Two independent blinded and trained measurers are going to realize the risk stratification of the volunteers, using the protocols described into the literature review of Silva et al.^[39]^ Following this, clinical (cardiorespiratory parameters and autonomic modulation), physical [maximum isometric resistance (MIR), maximum isometric voluntary contraction (MIVC), cardiorespiratory fitness, and physical activity level], and biochemical [interleukin (IL)-6, TNF-alpha, and IL-10] parameters are going to be evaluated by a blinded and trained measurer and the subjects are going to be accompanied during 24 sessions of their CRP routines, to register the appearance of their signals and symptoms.

In the second phase, the volunteers are going to realize their normal CRP routines for 6 months. In the third phase, the clinical, physical, and biochemical parameters, described above, are going to be evaluated by a blinded and trained measurer and the volunteers are going to be accompanied for more 24 sessions of their CRP routines, to register the appearance of their signals and symptoms as well.

The description of the phases and the volunteers that will be included in each one of them are reported at Fig. 1.

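### The method named for the change objective compares parameters between phases and leaves signs and symptoms out, so it cannot show whether parameter change is related to symptom change

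*Protocol article*

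**What the plan says.** The Introduction (protocol article, section 1) sets the aim: "to evaluate whether changes in clinical, physical, or biochemical parameters, induced by CRP, will influence the appearance of signals and symptoms during these programs". The Objectives in the Abstract state the same aim, without attributing the changes to the programme.

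Section 2.4 (Study design) measures the parameters in phase 1 and again in phase 3, with six months of usual rehabilitation between. Signs and symptoms are recorded over 24 sessions in phase 1; in phase 3 the patients are "accompanied for more 24 sessions of their CRP routines, to register the appearance of their signals and symptoms as well".

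Section 2.12 (Data analysis) begins the relevant paragraph with the aim: "To evaluate whether the clinical, physical, and biochemical modifications have influenced in the occurrence of signals and symptoms, the sphericity of the data". It then names the variables: "The comparison between the different moments of the clinical (cardiorespiratory parameters and autonomic modulation), physical" measures, "and biochemical (IL-6, TNF-alpha, and IL-10) are going to be realized by repeated measures analysis of variance (ANOVA"). It closes with "the possible differences between the moments will be performed by Bonferroni post-hoc".

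Elsewhere in section 2.12, symptom counts are related to the risk stratification grade ("The relationship between the number of signals and symptoms of the patients and the scale degree of the protocols (1, 2, and 3") by Pearson correlation and an intraclass correlation. ROC curves use the stratification protocols and the parameters as predictors of signs and symptoms.

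**The concern.** The aim asks about an association between two changes within the same patient: does a patient whose parameter moves also show a move in signs and symptoms? The method attached to it has only one of the two variables. Whatever the ANOVA shows, the question stays open.

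At stake is one of the study's stated aims. The data it needs are collected in both phases, but the plan specifies no analysis that joins them. Because the paragraph opens with the aim and ends with the ANOVA, a reader of the results could also take a shift in parameter means as an answer about symptoms.

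**Working it through.** **1. Which variables enter which analysis (section 2.12)**

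| Stated analysis | Sign/symptom variable? | Change in a parameter? | Change in symptoms? |
|---|---|---|---|
| Pearson, count against risk grade | yes | no | no |
| Intraclass correlation, protocol against count | yes | no | no |
| ROC, protocols and parameters as predictors | yes | no | no |
| Repeated-measures ANOVA, parameters between moments | no | yes (mean only) | no |

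No row has both changes. The only row that involves a change is the one with no symptom variable.

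**2. What the ANOVA reduces to.** Section 2.4 gives two measurement moments. With two levels there is one within-patient difference, so the ANOVA F is the square of the paired t. It tests whether the mean of (phase 3 minus phase 1) is zero.

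**3. The plan's own figure.** Section 2.2 gives SD 17 ms (rMSSD), alpha 5%, 80% (read as power) and N = 44, but no difference to detect, so 44 cannot be reproduced. Solving backwards, and assuming a two-sided paired test with 17 ms as the SD of the change:

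delta = 17 × (1.960 + 0.842) / √44 = 17 × 2.802 / 6.633 = 7.18 ms, or 7.18 / 17 = 0.42 SD.

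This serves only as a plausible shift for the next step.

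**4. Does the planned test respond to the association?** Assumed: n = 44, normal changes, SD of change 17, two-sided 5%, 4,000 simulated studies per setting. The table gives the percentage rejecting.

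| True correlation of changes | Planned test, no mean change | Planned test, mean change 7.18 ms | Change-on-change correlation (range over both shifts) |
|---|---|---|---|
| 0 | 4.4 | 79.9 | 4.2 to 5.1 |
| 0.3 | 5.5 | 77.9 | 51.0 to 52.0 |
| 0.41 | 4.7 | 78.6 | 79.6 to 80.2 |
| 0.6 | 4.7 | 78.7 | 99.4 to 99.5 |

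The planned test's columns are flat apart from simulation error. They depend on the mean shift alone. For other assumed shifts the paired test's power at n = 44 (noncentral t) is about 10% at 0.1 SD, 25% at 0.2, 49% at 0.3, 78% at 0.42 and 90% at 0.5, and the correlation enters none of these.

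**5. What 44 patients could detect if the right question were tested.** By Fisher's z, r = tanh(2.802 / √(n − 3)). The smaller n are assumptions about losses.

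- n = 44: tanh(2.802 / 6.403) = tanh(0.438) = 0.41
- n = 40: 0.43
- n = 35: 0.46
- n = 30: tanh(2.802 / 5.196) = tanh(0.539) = 0.49

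**6. How many parameters.** Section 2.7 lists 10 cardiorespiratory measures (blood pressure counted once). Section 2.7.3 gives 10 heart rate variability indices (two time-domain, five frequency-domain, three Poincaré), section 2.8 has 4 physical measures and section 2.9 has 3 cytokines. That makes 10 + 10 + 4 + 3 = 27, so about 27 × 0.05 = 1.35 nominally significant results are expected if none is related to symptom change.

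**The case against.** The best defence is that showing the parameters changed is a legitimate first step, and that a journal article condenses its plan. The first half stands: the paired comparison is worth keeping as description. The second does not help, because the article does not leave the method open. It names one for this aim, and that method addresses a different question.

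Three stronger readings are tempting, and the documents do not support them.

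- A reader might infer that the phase 3 symptom record goes unused. The Pearson, intraclass correlation and ROC analyses are not restricted to phase 1, so phase 3 counts may enter them. What can be said is that no stated analysis compares the phases or relates the two changes.
- A reader might infer that a significant ANOVA will be reported as proof of influence, and a null one as proof of none. The article states no such decision rule. The misreading is a risk created by the paragraph's opening words, not something the plan prescribes.
- A reader might count the Mauchly test, the Greenhouse-Geisser correction and the Bonferroni step as further errors. With two moments sphericity holds trivially and there is one contrast, so they are redundant but alter no result.

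The phrase about changes induced by the programme is causal wording for an uncontrolled cohort. Section 2 openly calls the study observational, so this is a matter of how results are described and not a second defect of the same weight.

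**Conclusion.** The point holds. For the aim of relating parameter change to signs and symptoms, section 2.12 specifies an analysis without signs or symptoms in it, and nothing else in the article fills the gap. The result would carry no information on the association asked about: its rejection rate is the same at a true correlation of 0 and of 0.6.

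This conclusion is structural and rests on the variables listed in section 2.12 and the two measurement moments in section 2.4. The simulated percentages illustrate it under assumed shifts and normal changes; they do not estimate an effect in this study. The detectable correlation of 0.41 assumes all 44 patients are analysed.

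**What to change.** In section 2.12, keep the paired comparison and label it as a description of parameter change. Add, as the analysis for this aim, one model per parameter with signs/symptoms as the outcome. Choose one of two forms in advance.

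- **Difference regression.** Regress each patient's change in sign/symptom rate per attended session (phase 3 minus phase 1) on the change in the parameter, adjusted for the baseline parameter value.
- **Count model.** Use GEE or a mixed model with a log sessions-observed offset, containing phase, the baseline parameter, and the parameter change coded as 0 in phase 1 and as the observed change in phase 3. This coding matters: a change entered as a constant patient covariate would also be fitted to phase 1 symptoms, which precede it.

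The first works on an additive scale and the second on a multiplicative one, so they are not equivalent. Either way, use sessions attended as the denominator: section 2.1 excludes only patients below 30% attendance, so the number observed may differ between patients.

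State that results are associations, because the cohort has no control group, and that they are exploratory across some 27 parameters. State the precision: 80% power (two-sided 5%) for a correlation of about 0.41 with 44 patients, or about 0.49 if only 30 are analysed. Dropping Mauchly, Greenhouse-Geisser and Bonferroni is optional tidying.

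The cost is a rewritten paragraph and modest extra analysis, with no new patients or measurements.
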